##### **9.2. Analysis Populations**

The primary efficacy **and safety** population will consist of all randomized subjects who **were dispensed** at least one dose of blinded study drug *<letter, sentence, paragraph deleted>* irrespective of any *<letter, sentence, paragraph deleted>* deviations from the protocol or premature discontinuation.

*<Letter, sentence, paragraph deleted>.*

#### June 13, 2003 – Amendment 4

##### **9.3. Efficacy Parameters**

#### June 13, 2003 – Amendment 4

##### **9.3.1. Primary Efficacy: Time to the Occurrence of Major Cardiovascular Events**

*<Letter, sentence, paragraph deleted>The time to occurrence of a major cardiovascular event (CHD death, non-fatal myocardial infarction, resuscitated cardiac arrest, fatal or non-fatal stroke) is defined as the period of time elapsing between the first day of blinded study drug dispensed and the first day of documented occurrence of the major event.*

#### June 13, 2003 – Amendment 4

*<Letter, sentence, paragraph deleted from 9.3.2 thru 9.5.4.2>*

### **9.3.2. Secondary Efficacy: Definitions**

#### **9.3.2.1 Other Cardiovascular Morbidity and Mortality**

*The time to occurrence of the following events will be calculated as the period of time elapsing between the first day of blinded study drug dispensed and the first day of documented occurrence of:*

- a. Major coronary event (CHD death, non-fatal myocardial infarction, or resuscitated cardiac arrest).*
- b. Any coronary event (major coronary event or, CABG, PTCA, other revascularization procedure, procedure-related myocardial infarction or documented angina)*
- c. cerebrovascular event (fatal or non-fatal stroke, TIA)*
- d. peripheral vascular disease (PVD)*
- e. hospitalization with primary diagnosis of CHF*
- f. any cardiovascular event (any of the above)*

#### **9.3.2.2 All Cause Mortality**

*The time to occurrence of all cause mortality will be calculated as the period of time elapsing between the first day of blinded study drug dispensed and the day of documented occurrence of death.*

### **9.4. Methods of Analysis**

*All hypothesis testing will be two-sided at a significance level of 0.05 unless otherwise indicated.*

*Subjects who discontinue study medication will continue to be followed to assess the time to occurrence of each endpoint. Subjects who do not experience endpoints during the trial will be considered censored at the time of the data cut-off, death or last contact, whichever is earliest.*

#### **9.4.1. Primary Efficacy Analysis**

*The null hypothesis that there is no difference in the time to occurrence of a major cardiovascular event between the two treatment groups will be examined using a log rank test. The product limit estimates for the time to occurrence will be calculated and displayed graphically as “survival” curves.*

#### **9.4.2. Secondary Efficacy Analysis**

*A log rank test will be used to examine the differences in time to occurrence between the two treatment groups for the other cardiovascular morbidity and mortality variables and all cause mortality.*

*Risk ratios and 95% confidence limits will be estimated for the primary and secondary efficacy endpoints using Cox regression.*

### 9.4.3. Covariate and Subgroup Analyses

*Cox regression models will be used to examine the treatment effect adjusted for various covariates, and to examine the treatment by covariate interaction effects. Covariates to be examined include age, gender smoking status, presence or absence of diabetes, baseline triglycerides, baseline HDL, baseline LDL, CHF, other prevalent pre-existing condition categories of the study cohort, and prevalent concomitant medication use (such as hormone replacement therapy, aspirin, beta-blockers, calcium channel blockers, etc.). In addition, the above analyses will be used to examine subgroups of interest as specified above, such as women and revascularized patients.*

### 9.5. Safety Parameters

*Adverse events will be coded and grouped by body system. The incidence of adverse events reported during the study will be tabulated according to the number of affected patients as well as the number of events. The intensity and relationship to study drug of adverse events will also be summarized by body system and treatment groups.*

*The incidence of shifts from normal at baseline to abnormal at study completion will be summarized both overall and by direction for all safety laboratories by treatment group.*

*In addition, changes in serum lipid levels after 1, 2, 3, 4 and 5 years of treatment will be calculated for each treatment group both as percent change from baseline (the average of the values at Visit 4 and Visit 5) and as percent change from Visit 2. Serum lipids include total cholesterol, LDL, HDL, triglycerides, apolipoproteins A1 and B, and non-HDL. Further analysis to determine the relationship between the occurrence of endpoints and these lipid parameters will be investigated.*

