Atorvastatin is a new HMG-CoA reductase inhibitor that is available for clinical use at 10-80 mg/day (see reference (29) for review). Atorvastatin has an absolute bioavailability of 12%. It is highly protein bound ( $\geq 98\%$ ) and undergoes extensive first-pass metabolism in the liver as seen with other lipophilic statins. Metabolism of the parent compound though P450 3A4 produces pharmacologically active ortho- and para-hydroxylated metabolites. The  $t_{1/2}$  of atorvastatin is approximately 12 hours and extends to 20-30 hours when including active metabolites. Elimination is predominantly hepatic with hepatic impairment resulting in significantly increased AUC values. Renal impairment has no effect on pharmacokinetic parameters.

In short-term dose-response studies, atorvastatin has been shown to provide mean reductions of approximately 40-60% in LDL-C and 15-40% in triglycerides (TG). The 10 mg starting dose of atorvastatin has been shown to provide superior LDL-C and TG lowering than other statins. After 52 weeks of treatment at 80 mg/day, mean reductions in LDL-C and TG were 52% and 33%, respectively, in 189 severely hypercholesterolemic patients; these reductions were greater than those observed with 40 mg of simvastatin in combination with 20 grams of colestipol. The superior reductions in LDL-C and TG seen with atorvastatin are hypothesized to be a result of a more constant inhibition of HMG CoA reductase, greater decrease in intracellular cholesterol levels and decreased production and secretion of VLDL particles. This explanation is supported by the approximate 20% reduction in LDL-C observed with atorvastatin in receptor-negative homozygous FH patients.

The safety profile and toleration of atorvastatin appears to be similar to other statins. Discontinuation of therapy due to drug-related adverse events was <2% in clinical trials. The predominant clinical adverse effect appears to be of low frequency and gastrointestinal in nature. Raised serum transaminase levels occurred in 0.7% of patients

in clinical trials and, like other statins, appeared to be dose-related ranging from 0.2% at 10 mg to 2.3% at 80 mg. No confirmed cases of myopathy (confirmed CPK elevations >10 times the upper limit of normal with muscle symptoms) were seen in 2,502 patients treated in clinical trials.

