##### **6.4.1.1. Clinically Important Laboratory Abnormalities**

The following laboratory abnormalities are arbitrarily designated as clinically important and therefore are to be reported as adverse events.

- CPK > 10 times the ULN at 2 consecutive measurements 4 to 10 days apart accompanied by muscle tenderness or weakness (patients should be advised to report promptly unexplained muscle pain, tenderness, or weakness, especially if accompanied by malaise or fever).
- ALT/AST > 3 times the ULN at 2 consecutive measurements 4 to 10 days apart.

If either of the above abnormalities occur, the ~~letter, sentence, paragraph~~ Pfizer study manager or clinical monitor (or their designees) should be contacted immediately.

If at any time during the study the patient's ALT or AST levels increase to  $>3 \times$  ULN range, the patient should be scheduled for a repeat laboratory measurement within 1 week ( $\pm 3$  days). If the repeat value is still  $>3 \times$  ULN range, the patient should have their double-blind medication discontinued but should continue their participation in the study for the identification of clinical end points (see Section 6.6).

If at any time during the study, a patient either:

- reports unexplained muscle pain, tenderness, or weakness (especially if accompanied by malaise or fever), or
- their CPK level increases to  $>10 \times$  the ULN,

study medication should be temporarily discontinued and CPK measurements performed by the central laboratory within 1 week ( $\pm 3$  days). If the repeat CPK levels are  $> 10 \times$  the ULN with muscle pain, tenderness or weakness, the patient should have their double-blind medication discontinued but continue their participation in the study for identification of clinical end points (see Section 6.6).

Following normalization of a clinically important laboratory abnormality considered causally related to atorvastatin, the patient may be rechallenged with study medication. Rechallenges must be discussed with, and approved by, the ~~letter, sentence, paragraph~~ Pfizer clinical monitor (or their designee) and appropriate IRB/EC. These patients will maintain their original treatment group assignment during rechallenge. A rechallenge is defined as reinstitution of study drug following discontinuation for a medically significant adverse event considered to be caused by atorvastatin. (See Section 6.4.2.3 for further details)

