#### 9.6.1. Timing, Content

*Interim analyses to examine **primary** efficacy <letter, sentence, paragraph deleted> will begin after a median of 3 years of follow-up. The timing and number of interim analyses will be at the discretion of the DSMB.*

The interim analyses will include analyses of recruitment, subject characteristics, the primary efficacy and safety variables, all-cause mortality, and adverse events.

#### June 13, 2003 – Amendment 4

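### The only laboratory analysis specified in section 9.5, a baseline-to-completion shift, misses enzyme elevations that stopped study drug and resolved, and so understates any 80 mg versus 10 mg difference

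*Supplement*

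**What the plan says.** Section 9.5 (Safety Parameters) has two routes for laboratory harm.

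- **Laboratory values.** "The incidence of shifts from normal at baseline to abnormal at study completion will be summarized", overall and by direction, for all safety laboratories by treatment group. No any-time, worst-value or threshold summary is given.
- **Adverse events.** "The incidence of adverse events reported during the study will be tabulated according to the number of affected patients" as well as by number of events, with intensity and relationship to drug summarised by body system and treatment group.

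Section 6.4.1.1 links the two: "The following laboratory abnormalities are arbitrarily designated as clinically important and therefore are to be reported as adverse events". The transaminase criterion is "ALT/AST > 3 times the ULN at 2 consecutive measurements 4 to 10 days apart". The CPK criterion is more than 10 times ULN, confirmed, with muscle symptoms. If the repeat ALT or AST is still above 3 times ULN, "the patient should have their double-blind medication discontinued but should continue their participation in the study". A repeat CPK above 10 times ULN with symptoms has the same consequence.

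Section 6.7 places study completion at the accrual of 750 major coronary events, which section 6.1 expects at about 5.5 years of average follow-up. Exclusion criterion 1b in section 5.2.2 rules out ALT or AST of 1.5 times ULN or more, so a patient between 1 and 1.5 times ULN may be randomised. The Introduction describes raised transaminases as a known effect of the drug that "appeared to be dose-related ranging from 0.2% at 10 mg to 2.3% at 80 mg".

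**The concern.** The stopping rule and the analysis rule work against each other. Patients with the most important elevations are taken off drug. Their completion sample may come years later, usually off drug, and reads as normal if the elevation has resolved. The table then counts them with patients who never had an abnormal value. A patient slightly above normal at baseline cannot enter a normal-to-abnormal shift however far the value later rises. The Visit 6, Visit 9, annual, repeat and rechallenge results enter only if one happens to be the completion value.

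The safety profile of the more intensive strategy is a stated objective (Synopsis; section 2), and the transaminase effect is the laboratory signal that the protocol itself expects to differ by dose. A summary that shrinks that difference could be read as reassurance that the data do not give.

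**Working it through.** The protocol gives no figure for the laboratory analysis, so there is none to reproduce. The check is a reading of the text followed by arithmetic for scale.

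**How one patient is counted.** Take a patient with normal ALT at baseline, a confirmed ALT above 3 times ULN in year 1, drug stopped under section 6.4.1.1, and a normal ALT at trial end.

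- Shift table (9.5): normal to normal, not counted.
- Adverse-event table (9.5): counted, if reported by the site, under whatever coded term and body system is assigned.
- A threshold incidence by arm from the central laboratory: not specified.

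If the same patient had started at 1.3 times ULN, the shift table could not count the rise, whether or not it resolved.

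**Inputs.**

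- Randomised patients: about 8,600 (section 5.1). The assumption of 1:1 allocation gives 4,300 per arm.
- Raised transaminases: 0.2% at 10 mg and 2.3% at 80 mg (Introduction), with no threshold or exposure time stated.
- f, the share of affected patients still abnormal at completion: the documents give none, so the full range is shown, with f taken as equal in the two arms.

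**Expected numbers affected at any time.**

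- 80 mg: 4,300 × 0.023 = 98.9
- 10 mg: 4,300 × 0.002 = 8.6
- Excess: 98.9 − 8.6 = 90.3 patients, or 2.1 percentage points

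**What those patients add to the shift table**, count = 4,300 × rate × f:

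| f | 10 mg | 80 mg | Excess |
|---|---|---|---|
| 0 | 0 | 0 | 0 |
| 10% | 0.9 | 9.9 | 9.0 |
| 25% | 2.2 | 24.7 | 22.6 |
| 50% | 4.3 | 49.5 | 45.2 |
| 100% | 8.6 | 98.9 | 90.3 |

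The risk difference in the shift table is f × 2.1 points. It is attenuated for every f below 1. With equal f the ratio of these counts is unchanged, but the table also counts mild abnormalities unrelated to dose. If 5% of each arm were abnormal at completion for other reasons (an assumption), f = 10% gives 215 + 9.9 = 224.9 versus 215 + 0.9 = 215.9. That is a ratio of about 1.04.

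**What an any-time count would give on the same rates.** Standard error = √(0.023 × 0.977/4,300 + 0.002 × 0.998/4,300) = 0.00239. The 95% CI is 2.1 ± 1.96 × 0.239 points, or about 1.6 to 2.6 points. A two-sided 5% comparison of the two proportions would have power above 99.9%.

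The documents give no dose-specific rate for CPK elevation, so the arithmetic covers transaminases only. The reasoning from the text applies to both.

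**The case against.** The strongest reply is that the adverse-event route already captures these patients. Sections 6.4.1 and 6.4.1.1 require the confirmed elevations to be reported as adverse events, the sponsor must be contacted at once, and Appendix D section 1.3 adds any test result that leads to a change in dosing. Section 9.5 then counts affected patients. This stands. A reader might infer that the elevations disappear from safety reporting, and the documents do not support that. What remains is that the adverse-event table depends on site reporting and coding, and that no threshold incidence by arm is specified.

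A second reply is that worst-value tables belong in a separate analysis plan, which is not shown. That would answer a complaint about missing detail. Here the protocol makes a positive choice of laboratory summary, and that choice can be judged.

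Third, section 9.5 does not define study completion for this table. Section 6.6 requires end-of-study procedures when drug is stopped early, and using those samples would catch some elevations. Rechallenge also means that some patients are back on drug at the end. Sections 6.6 and 6.7 nonetheless use study completion to mean the end of the trial, and section 9.5 does not say that early-stop samples are used.

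Fourth, a reader might infer from section 9.6.1, which lists "the primary efficacy and safety variables, all-cause mortality, and adverse events" for interim review, that the DSMB is pointed to a primary safety variable that does not exist. The phrase can equally mean primary efficacy variables together with safety variables, so nothing is built on it here.

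**Conclusion.** The point holds as a defect of the specified laboratory summary. The rule in section 9.5 cannot register elevations that stopped drug and resolved by trial end, nor any rise in patients above normal at baseline, and this biases the arm comparison towards no difference. On the protocol's own rates about 9 versus 99 patients are at issue. The shift table would retain 0 versus 0 at f = 0, about 1 versus 10 at f = 10%, and 9 versus 99 at f = 100%.

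The size rests on 4,300 patients per arm and on background rates from other trials. Those rates have no stated threshold, and this trial randomises only patients who tolerated the 10 mg run-in. A reader might settle on one figure, such as an excess of 90 shrinking to between 9 and 18. That needs 80–90% of elevations to normalise, a share that the documents do not supply. The direction of the bias does not depend on the rates; it needs only that some elevations resolve.

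This should be fixed, but it does not threaten the trial. The efficacy analysis and the mortality monitoring boundary are unaffected, and the adverse-event tables give partial cover.

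**What to change.** Add to section 9.5, by treatment group:

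- the number and proportion of patients who, at any time after randomisation, have ALT or AST above 3 times ULN on two consecutive tests, using the section 6.4.1.1 definition and central-laboratory data, with risk difference and 95% CI;
- the same for CPK above 10 times ULN with muscle symptoms, again as defined in section 6.4.1.1;
- for the other safety laboratories, the worst post-baseline value by baseline category, so that patients abnormal at baseline are included.

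Keep the baseline-to-completion shift as a supplement, and state in section 9.5 which sample counts as study completion for a patient who stopped drug early.

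The cost is a short paragraph and one additional table. The measurements are already collected by the central laboratory, the thresholds are the protocol's own, and patient management does not change.

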### 9.6. Interim Analyses

#### June 13, 2003 – Amendment 4

#### 9.6.1. Timing, Content

*Interim analyses to examine **primary** efficacy <letter, sentence, paragraph deleted> will begin after a median of 3 years of follow-up. The timing and number of interim analyses will be at the discretion of the DSMB.*

The interim analyses will include analyses of recruitment, subject characteristics, the primary efficacy and safety variables, all-cause mortality, and adverse events.

#### June 13, 2003 – Amendment 4

#### 9.6.2. Early stopping

The *log-rank* statistic for the hypothesis test of the null hypothesis of no difference in the probability of occurrence of major **cardiovascular** events between atorvastatin 10 and 80 mg groups will be compared to the critical boundary values *based on a two-sided Peto type monitoring boundary with a critical value (Z) of  $\pm 3.0$* . If the group sequential boundary is crossed, then the DSMB will consider a recommendation to stop the trial.

However, actual stopping of the trial is a complex decision involving a number of factors besides the simple comparison of one statistic with one critical value. The DSMB will take all the data together and analyze the data in concert including performing additional analyses before making a recommendation that the trial be stopped. A partial list of factors besides the magnitude of an apparent treatment effect that should be taken into account include the clinical significance of an apparent effect, whether an apparent effect could be explained by baseline imbalance or concomitant therapy, whether occurrence of major coronary events is consistent with other signals in the data, whether results are consistent within subgroups and centers, the likelihood of a reversal in the current trend, and the needs of the medical research community and future patients for a definitive answer to the research questions.

***Interim monitoring for harm will be based on all-cause mortality using a log-rank test with an O'Brien-Fleming boundary (two-sided  $\alpha = .05$ ) truncated to  $\pm 3.0$ . If the group sequential boundary is crossed, then the DSMB will consider a recommendation to stop the trial. The DSMB will take all the data together and analyze the data in concert including performing additional analyses before making a recommendation that the trial be stopped for harm.***

In summary, a recommendation to modify or terminate the trial would not be based totally on the crossing of a group-sequential boundary.

***<Letter, sentence, paragraph deleted>***

### **9.6.3. Distribution of the interim analysis**

A limited number of copies of the report containing the interim analyses will be produced. They will be numbered, and they will be collected after each meeting. Only those individuals on the DSMB will have access to the results.

## **10. ECONOMIC ANALYSES**

Descriptive summaries of health care outcomes will be reported. These summaries include but are not limited to: rate of CV hospitalizations and revascularization procedures, total number of hospital days, time to first hospitalization and time to first revascularization procedure.

## **11. DNA Databank**

### **11.1 INTRODUCTION**

New developments in molecular biology have directed research of human disease towards its genetic basis. The understanding of the molecular origin of a disorder and the insight into the way genetic information is expressed or modulated by the environment will have a major impact on treatment and prevention of disease. It is estimated that the genetic predisposition for atherosclerotic disease involves more than 200 genes. The exact role in the atherosclerotic process is only known for a small number of genes. These genes play an important role in the aetiology of atherosclerotic disorders such as coronary heart disease (CHD), as has been shown in a large number of studies. The use of large, well documented

patient cohorts has enabled the identification of new genetic risk factors for CHD. The aim of the DNA databank is to establish the relationship between a number of genetic markers, known to influence cardiovascular risk in the general population, and the clinical phenotype and response to lipid lowering therapy in patients with pre-existing cardiovascular disease.

**June 13, 2003 – Amendment 4**

**11.2. PROCEDURE**

At Visit 5 or the first possible visit at which blood is collected post-randomization, 12 mls of whole blood will be collected into plastic tubes containing EDTA from randomized subjects who consent to undergo additional genetic testing. Refusal to participate in the additional testing will not effect the subject's participation in the main study. After collection and labeling of the sample, the whole blood sample with the other biochemical samples collected during this visit will be mailed to:

[REDACTED] or [REDACTED]  
ATTN: [REDACTED]  
[REDACTED]  
[REDACTED]

